### Suicide risk

Suicidality will be assessed using the Columbia-Suicide Severity Rating Scale (C-SSRS), a semi-structured clinical interview used to measure suicidal behavior [59]. This assessment requires additional follow-up questions based on the veterans’ responses; thus, this task will be administered via computer or tablet with the guidance of the administrator.

#### Complementary outcome measures

For a summary of complementary measures, see Table 5.

**Table 5 Tab5:** Data Collection Summary for Complementary Outcome Measures

	Enrollment	Baseline	1 Week	Post-treatment
**Supplemental Cognitive-Behavioral Measures (Aim 2)**				
CNS Vital Signs (VBM, VIM, FTT and POET Subtests)		X	X	X
**Exploratory Cognitive-Behavioral Measures (Aim 2)**				
*Executive Functioning*				
Trail Making Test A and B ^a^		X		X
Wechsler Adult Intelligence Scale-4th edition (WAIS-IV): Coding Subtest ^a^		X		X
Wechsler Adult Intelligence Scale-4th edition (WAIS-IV): Digit Span Subtest		X		X
Delis-Kaplan Executive Function System (D-KEFS): Color-Word Interference Subtest ^a^		X		X
Delis-Kaplan Executive Function System (D-KEFS): Verbal Fluency Subtest- Standard Form		X		
Delis-Kaplan Executive Function System (D-KEFS): Verbal Fluency Subtest- Alternate Form				X
*Verbal and Nonverbal Memory Functioning*				
California Verbal Learning Test-Third Edition (CVLT-III)- Standard Form		X		
California Verbal Learning Test-Third Edition (CVLT-III)- Alternate Form				X
Brief Visuospatial Memory Test-Revised (BVMT-R): Form 1 ^a^		X		
BVMT-R: Alternate Form 2 ^a^				X
*Motor Functioning*				
Grooved Pegboard ^a^		X		X

This table describes the schedule of each complementary test. Data collection occurs at 4 time points as shown above. Enrollment and Baseline research sessions occur prior to the commencement of TMS treatment session 1. The 1 Week research session occurs after completion of the first TMS treatment sessions within the first week, targeting the first 5 TMS sessions. The Post-treatment research session occurs after completion of TMS treatment, targeting 30 TMS sessions. ^a^These assessments may be altered or not administered if teleneuropsychological administration is conducted

##### Supplemental cognitive-behavioral measures

As described above (see CNS Vital Signs), four subtests of the CNS Vital Signs Battery will be used as supplemental measures to control for potential confounding variables, such as motor speed, memory, and perception.
**Verbal Memory (VBM):** A measure of recognition memory for words. Fifteen words are presented, one by one, on the screen every two seconds. For immediate recognition, the veteran must identify those words nested among fifteen new words. Then, after six more tests, there is a delayed recognition trial.**Visual Memory (VIM):** Measures recognition memory for figures or shapes. Fifteen geometric figures are presented, one by one, on the screen. For immediate recognition, the veteran must identify those figures nested among fifteen.**Finger Tapping (FTT):** This test requires subjects to press the spacebar with their right index finger as many times as they can in ten seconds. They do this once for practice, and then there are three test trials. The test is repeated with the left hand.**Perception of Emotions (POET):** Measures how well a subject can perceive and identify specific emotions.

##### Exploratory neurocognitive measures

A brief neuropsychological evaluation will be administered for the purpose of future clinical translation. We will attempt to administer these assessments in-person using an internally certified neuropsychology trainee or research coordinator. However, under public health circumstances in which assessments may have to be conducted remotely, we will use teleneuropsychological administration. Teleneuropsychological administration is considered an appropriate alternative for several cognitive measures that will be used within this study [28, 60–62] and will be guided by best practices [27, 29, 30, 63, 64]. Certification requires attending a training seminar developed by a licensed clinical neuropsychologist, being cleared by the neuropsychologist or the appropriate proxy who is supervised by the neuropsychologist to administer each measure, and attending quarterly supplemental refresher courses. The cognitive measures were selected in order to capture general cognitive functioning within the specific domains of memory, attention, language, executive functioning, motor functioning, and visuoperceptual abilities. The neuropsychological battery will be altered to use alternate forms when available depending on the assessment session. Specifically, veterans will be given alternative test stimuli at the Post-treatment research session in order to help alleviate concerns regarding practice effects and test-retest reliability. Published reliable change indices will be utilized to detect clinically meaningful change for tests where alternate test forms are unavailable. Table 5 provides a summary of additional exploratory measures administered in this study.

Administrators will use test-specific normative data to convert veterans’ raw scores into standardized scores. Each site will also attempt to use the same testing administrator at both Baseline and Post-treatment research sessions in order to avoid individual differences in test administration and scoring. Sites will be encouraged to have a second person score each measure to ensure accuracy.

***Executive Function***
**Trail Making Test A and B**: A measure of processing speed, sequencing, mental flexibility and visual–motor skills [65]. Standardizing raw scores will be accomplished using the Revised Comprehensive Norms for an Expanded Halstead-Reitan Battery: Demographically Adjusted Neuropsychological Norms for African American and Caucasian Adults [66]. We will use the reliable change indices from Dikmen et al. [67]. If teleneuropsychological administration is conducted, Oral Trails [68] may be used as a modification to the Trail Making Test A and B.**Wechsler Adult Intelligence Scale-4th edition (WAIS-IV) – Selected Subtests**: A measure of processing speed (i.e., Coding) and simple and complex auditory attention (i.e., Digit Span) [37] will be administered. Standardized scores and reliable change indices will be obtained using the normative data from the WAIS-IV Examiner’s and Technical Manuals. If teleneuropsychological administration is conducted, Coding may not be administered.**Delis-Kaplan Executive Function System (D-KEFS) – Selected Subtests**: A measure of visual processing speed and cognitive control will be administered (i.e., Color-Word Interference). A measure of lexical fluency, semantic fluency, and executive control will also be administered (i.e., Verbal Fluency Subtest (VF), Standard and Alternate Form) [69]. The VF-Standard Form will be administered at Baseline, while the VF-Alternate Form will be given at the Post-treatment Visit. Standardized scores and reliable change indices will be derived from the D-KEFS Examiner’s and Technical Manuals. If teleneuropsychological administration is conducted, slight modifications will be used for the Color-Word Interference subtest.***Verbal and Nonverbal Memory Function***
**California Verbal Learning Test-Third Edition (CVLT-III)**- Standard and Alternate Form: The CVLT-III is a 16-item list assessment that measures verbal learning, memory, and recognition [70]. The Standard Form will be administered during the Baseline Visit, while the Alternate Form will be administered during the Post-treatment Visit. Normative data from the CVLT-III Examiner’s Manual will be used for standardizing raw scores.**Brief Visuospatial Memory Test-Revised (BVMT-R), Form 1 and Form 2**: The BVMT-R is an assessment used to measure visuospatial learning and memory [71]. Form 1 will be administered at Baseline and Form 2 will be given at the Post-treatment Visit. Standardized scores will be derived from the BVMT-R Examiner’s Manual. If teleneuropsychological administration is conducted, slight modifications will be made for this measure.***Motor Function***
**Grooved Pegboard**: The Grooved Pegboard is a measure of eye-hand coordination and motor speed and often used to localize deficits [65]. Standardized scores will be derived from the Revised Comprehensive Norms for an Expanded Halstead-Reitan Battery: Demographically Adjusted Neuropsychological Norms for African American and Caucasian Adults [66] and reliable change indices will also be used [67]. If teleneuropsychological administration is conducted, Grooved Pegboard may not be administered.

## Regular care TMS protocol within the partner clinical TMS program of the VA

Veterans will receive TMS treatment as part of their regular clinical care within the VA. Because we will utilize the umbrella VA Clinical TMS Program, we can ensure that the parameters received by veterans are uniform. Treatment will be delivered using the Magstim Rapid 2 or Magstim Horizon Performance devices (The Magstim Company Ltd., Whitland, United Kingdom).

At the time of study design, current clinical practice standards for MDD indicate one session of TMS per day five times per week for 6 weeks. This protocol assumes a magnetic field intensity of 120% of motor threshold at a frequency of 10 Hz at the left DLPFC stimulation site. Treatment sessions take approximately 37.5 min resulting in 3000 pulses per treatment session delivered based on the following treatment parameters: train duration of 4 s, inter-train interval of 26 s, and 75 trains. Stimulation targets are reached through anatomical landmarks using the Beam-F3 method [72].

Depending on veteran treatment response and physician discretion, the standard TMS treatment protocol may be subject to change throughout the treatment course.

## Statistical analysis

### Power calculation

The sample size was calculated based on a conservative scenario in which we estimate a main effect for TMS on targets of interest of small effect size (Cohen’s d of approximately 0.25), and use a within-subjects linear model with session as a repeated measure, at least one moderator of interest (extent of baseline connectivity dysfunction) and three covariates. It is possible that effect sizes are larger. Dependent measures are connectivity, behavior, and self-report measures (3 measurement domains), and change in these measures, assessed in separate models. With an alpha level of 0.05 (two-tailed), power of 0.875 and an anticipated correlation of 0.5 for repeated sessions we require at least 98 veterans. To target 100 veterans and allow for the potential for dropout over the 3 sessions we aim to recruit 125 veterans. If a greater effect size is obtained, this would lead to greater power.

### Data analysis plan

We will pursue a stepwise analysis plan that starts with a focus on our a priori regions of interest and builds to a model based on machine-learning of these regions, and then an exploratory phase, as follows:

For *Aim 1*, we will quantify functional connectivity in the resting and task conditions by computing correlation coefficients between the a priori regions of interest and converting these coefficients to Fisher Z scores. In task-evoked conditions we will also use gPPI to quantify connectivity incorporating the task contrast. Multivariate linear mixed models will be used to test the hypothesis that extent of connectivity is a response biomarker determining extent of post-treatment change in both connectivity and in clinical measures after 1 Week of treatment and Post-treatment (within-subjects). We will include both binary between-subjects and continuous moderators to assess whether veterans with intact pre-treatment connectivity show connectivity change after early sessions whereas veterans with impaired pre-treatment connectivity show change after completion of sessions. Correlational analyses will be used to test whether the extent of early change is proportional to the extent of baseline connectivity impairment.

For *Aim 2*, we will use the connectivity values established under Aim 1. Linear mixed models, with behavioral measures included as dependent variables, will be employed to test the hypotheses that extent of connectivity relates to extent of behavioral performance and that change in connectivity predicts change in behavioral performance (within subjects). We will include binary and continuous moderators to test if these relationships differ as a function of degree of baseline connectivity dysfunction after 1 Week and after Post-treatment sessions.

For *Aim 3*, we will again use the connectivity values established under Aim 1. Linear mixed models, with symptom, function, and suicidality measures included as dependent variables, will be employed to test the hypotheses that extent of baseline connectivity predicts severity of symptoms, functional disability and suicidality and that change in connectivity predicts changes in symptoms, function, and suicidality (within subjects). We will include binary and continuous moderators to test if these relationships differ as a function of degree of baseline connectivity dysfunction for after the 1 Week and Post-treatment sessions.

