To evaluate a response biomarker of the effect of TMS on promoting cognitive control. We will assess whether activation and functional connectivity of the DLPFC-anchored cognitive control network, and interactions with sgACC, attention and default mode regions involved, change in a session (akin to dose)-dependent manner. Our broad hypothesis is that functional connectivity will change from the pre-treatment baseline to reassessment early after commencement of TMS (targeting 5 sessions) and later, post- completion of treatment (targeting 30 sessions). Related, we hypothesize that the early change will be most pronounced for patients with intact connectivity at baseline; later change post-treatment will be observed for those with more impaired baseline connectivity. First, we will address the mechanistic question of whether early changes in circuit connectivity are necessary, if not sufficient, for subsequent circuit and clinical changes observed post-TMS. Second, we will systematically test whether the extent of change in connectivity is related to the extent of dysfunction at the pre-stimulation baseline. Third, we will probe whether observed changes in connectivity increase as a session-dependent function of the total number of TMS sessions. In addressing these issues, we will incorporate a methodological technique to quantify the site of DLPFC stimulation with anatomical precision.

### Aim 2

To assess whether the extent of change in a DLPFC cognitive control network connectivity response biomarker is related to corresponding change in behavioral performance. Our broad hypothesis is that the extent of connectivity change will be related to the extent of change in behavioral performance, and that this relationship will be most pronounced for patients with relatively intact connectivity at baseline; later change will be observed in patients with more impaired baseline connectivity.

### Aim 3

To identify if pre-treatment functional connectivity of the DLPFC cognitive control network, involving interactions with the sgACC and regions of the attention and default mode networks, and behavioral performance, along with early change in connectivity and behavior, are predictive biomarkers of clinical outcome. Our hypothesis is that baseline connectivity and behavior, and early and later changes in these measures will predict who at post-treatment have the greatest change in symptom severity, suicidality, and quality of life.

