### Task-based fMRI and resting state

**GoNoGo**. We will use the GoNoGo task (depicted in Fig. 2) to assess response inhibition and cognitive control. Behavior is assessed in terms of “False alarm” NoGo errors and reaction time for Go stimuli. This task is well normed across nine decades [40], and has sound test-retest reliability, including parallel forms for repeat testing. It has been shown to robustly elicit inhibition errors in MDD and PTSD [15, 41]. In the GoNoGo task, veterans respond via button press as quickly and accurately as possible to Go stimuli (the word “Press” in green) and withhold responses to NoGo stimuli (the word “Press” in red). There are 180 Go and 60 NoGo stimuli (ratio 3:1), presented pseudorandomly with duration of 500 ms and jittered interstimulus interval of 750 ms.**N-Back Working Memory**. The N-Back working memory task (depicted in Fig. 2) has been used previously to probe working memory maintenance and sustained attention functions in depression [42]. Stimuli are presented under three conditions: 30 sustained attention stimuli in which yellow letters appear twice in a row and veterans respond to the consecutive yellow letter; 50 working memory stimuli in which yellow letters appear randomly and not consecutively and veterans are required to maintain and update working memory without responding to the letters; and 40 perceptual baseline stimuli in which to-be-ignored white letters are presented as a perceptual contrast to yellow letters. Working memory stimuli are not presented in a design that manipulates different levels of working memory demand.**Resting State.** Veterans will be instructed to stare at a white cross on a black background. During this time, their eyes will be monitored using an eye tracker by the study coordinator to ensure they are not asleep.

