**Secondary Outcomes - Cognitive-Behavioral Measures (Aim 2)**				
CNS Vital Signs Battery (SDC, Stroop, SAT, CPT Subtests)		X	X	X
Webneuro Abbreviated Version (GoNoGo and N-Back Subtests)		X	X	X

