### WebNeuro

Computerized tests of cognitive control performance will be measured offline using WebNeuro [51–53]. These tasks will be executed on a computer by the veteran at the Baseline, 1 Week, and Post-treatment research assessment sessions. The software used to run the tasks incorporates standardized task instructions. Psychometric properties have been established for each of these tests, including norms, construct validity, validation against traditional neuropsychological tests evaluating equivalent functions, test-retest reliability, and consistency across cultures [2]. For each test, we will record accuracy and reaction time.

**N-Back Task/Continuous Performance Test**: This is a measure of sustained attention. A series of 125 similar looking letters (B, C, D, or G) are presented to the veteran on the computer screen for 200 msec with an interval of 2.5 s between each letter. If the same letter appears twice in a row, the veteran is required to press the spacebar. There are 85 nontarget letters and 20 target letters (i.e. repetitions of the previous letter).**GoNoGo Task:** A word (press) is frequently presented in the color *green* (Go) and infrequently in the color *red* (NoGo). The veteran is asked to respond with a keypress when the word is presented in green and inhibit a keypress when it is presented in red. Inhibition is assessed with omission of keypress responses when the word ‘press’ is red.**Symbol Digit Coding (SDC):** This test consists of serial presentations of screens, each of which contains a bank of eight symbols above and eight empty boxes below. The veteran types in the number that corresponds to the symbol that is highlighted.**Stroop Test:** The Stroop test has three parts which measure simple and complex reaction time, inhibition, frontal skills, and processing speed.**Shifting Attention (SAT):** This test is a measure of ability to shift from one instruction set to another quickly and accurately. Veterans are instructed to match geometric objects either by shape or by color.**Continuous Performance (CPT):** This test is a measure of vigilance or sustained attention. The test subject is asked to respond to the target stimulus “B” but not to any other letter. The stimuli are presented at random.

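### The plain region-to-region correlation planned for task runs mixes co-activation with coupling; gPPI or a task-regressed correlation should be the task measure carried into Aims 2 and 3

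*Protocol article*

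**What the plan says.** All references are to the protocol article.

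- **Data analysis plan, Aim 1.** The plan says "we will quantify functional connectivity in the resting and task conditions by computing correlation coefficients between the a priori regions of interest", followed by conversion to Fisher Z. One method thus serves both rest and task. The next sentence adds: "In task-evoked conditions we will also use gPPI to quantify connectivity incorporating the task contrast". The word for gPPI is *also*, so it supplements the correlation and does not replace it.
- **Data analysis plan, Aims 2 and 3.** For Aim 2, "we will use the connectivity values established under Aim 1"; Aim 3 does the same. Neither says whether the task value is the correlation, gPPI or both.
- **Background, Aim 1.** Activation is a target in its own right: "We will assess whether activation and functional connectivity of the DLPFC-anchored cognitive control network", together with its interactions, is to be assessed for session-dependent change.
- **Interactions, covariates and cross-validation.** The covariates are sex, medication, medication change, comorbidity, substance use and premorbid function. None is activation or task performance.
- **Table 4.** The Aim 2 outcomes are four CNS Vital Signs subtests and the WebNeuro GoNoGo and N-Back subtests. The WebNeuro section says: "Computerized tests of cognitive control performance will be measured offline using WebNeuro". The in-scanner GoNoGo task also yields behaviour ("Behavior is assessed in terms of “False alarm” NoGo errors and reaction time for Go stimuli"), but Table 4 does not list that as an Aim 2 outcome.
- **Limitations.** The study has no control group.

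**The concern.** Two regions that both respond to the same stimuli share a time course, and that alone gives them a correlation, whether or not they are coupled. At rest there is no stimulus and the issue does not arise. In a task run it does, unless the evoked response is modelled and removed first.

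The plan treats activation and connectivity as separate targets and expects both to change, yet the plain task correlation responds to both. Every participant is scanned on the same tasks three times with no comparison group. A drift in activation from habituation or practice would therefore enter that measure in the same way as a treatment effect. The same values define the intact-versus-impaired baseline moderator and are passed to Aims 2 and 3. The plan's two task measures can give different answers to the same question, and the text does not say which one is the biomarker.

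**Working it through.** The plan gives no figure on this point, so there is nothing to reproduce. Three checks were made.

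**Inputs from the document.** GoNoGo run: 151 volumes, TR 2 s, 180 Go and 60 NoGo stimuli. Effect size used for sizing: d about 0.25.

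**Inputs assumed (none is in the document).** Share *s* of each region's variance due to the evoked response, 0 to 0.20; background correlation *r0*, 0 to 0.5; SD of Fisher Z, and of its change, 0.20.

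**Check 1: does the measure respond to activation when coupling is fixed?** If both regions carry the same evoked response with share *s*, then r = (1 − s)·r0 + s. With opposite-sign responses, r = (1 − s)·r0 − s. At r0 = 0.3 and s = 0.10 these give 0.27 + 0.10 = 0.370 and 0.27 − 0.10 = 0.170, so the bias can go either way. A simulation of a GoNoGo-like run (same-direction responses, r0 = 0.3, 400 runs per row) gave these means:

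| s | Z from formula | Plain Z | Z after task regression | gPPI contrast |
|---|---|---|---|---|
| 0 | 0.310 | 0.316 | 0.315 | 0.002 |
| 0.02 | 0.325 | 0.327 | 0.312 | 0.007 |
| 0.05 | 0.348 | 0.351 | 0.313 | 0.001 |
| 0.10 | 0.388 | 0.391 | 0.310 | 0.002 |
| 0.20 | 0.472 | 0.472 | 0.307 | 0.003 |

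The standard error of the gPPI column is about 0.005. The plain correlation moves with activation; the other two measures do not.

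**Check 2: how large is the shift between sessions?** Take a 50% relative rise in *s*, same-direction responses. Example: r0 = 0.3 and s from 0.10 to 0.15 takes r from 0.370 to 0.85 × 0.3 + 0.15 = 0.405, a change in Z of 0.041. All cases:

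| r0 | s 0.02 to 0.03 | s 0.05 to 0.075 | s 0.10 to 0.15 |
|---|---|---|---|
| 0 | 0.0100 | 0.0251 | 0.0508 |
| 0.3 | 0.0078 | 0.0198 | 0.0412 |
| 0.5 | 0.0068 | 0.0174 | 0.0366 |

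Divided by an SD of 0.20, the range is 0.0068/0.20 = 0.03 to 0.0508/0.20 = 0.25.

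**Check 3: how much could this add to the Aim 2 association?** At r0 = 0.3 and s = 0.05, r = 0.335 and dZ/ds = 0.70/(1 − 0.335²) = 0.788. Assume the change in *s* has SD 0.02 to 0.05 and correlates q = 0.2 to 0.4 with change in performance, and that true Z change has SD 0.20. The artefact then has SD 0.788 × 0.02 = 0.0158 to 0.788 × 0.05 = 0.0394. The induced correlation is q × artefact SD / √(artefact SD² + 0.20²):

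- low end: 0.2 × 0.0158/0.2006 = 0.016
- high end: 0.4 × 0.0394/0.2039 = 0.077

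This applies only if the unadjusted task correlation is the value entered in Aim 2.

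**The case against.** The strongest reply is that the standard remedy is already planned. gPPI models the task main effects and stayed near zero in the check above. The article also does not say that raw time series are correlated; task regression is a pipeline detail that a condensed article may leave to the full protocol or analysis plan, which are not shown. This stands in part. It limits the point to one of two task measures and leaves open that the pipeline already handles it. It does not remove the point, because the article positively states one correlation method for rest and task, makes gPPI an addition, and passes the values on without choosing between them.

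Three stronger readings are tempting and are not supported.

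- *Plain correlation is the only task measure.* The sentence on gPPI directly follows.
- *The Aim 2 association is built in by the way connectivity is derived.* The listed Aim 2 outcomes come from tests separate from the scanner runs. A link would have to pass through activation change that tracks separately measured ability. It remains plausible, since WebNeuro includes versions of the scanner tasks, but it is indirect.
- *Aim 2 faces a gross false-positive rate.* A rate of about 35% at n = 98 can be simulated, but only with an SD of change in *s* of 0.10 around a baseline of 0.10 and a correlation of 0.5 with behaviour change. Under a normal model about 16% of participants would then have a negative variance share, which is impossible. With SD 0.05 and correlation 0.3 the rate was about 8%, against a nominal 5%.

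**Conclusion.** The point holds for the unadjusted correlation in the GoNoGo and N-Back runs. As stated, that measure cannot separate a change in activation from a change in coupling, in an uncontrolled three-session design where activation is itself expected to change. For Aim 1 the possible shift runs from negligible to about the d of 0.25 on which the trial was sized. That range covers same-direction responses and a 50% relative rise in evoked share; opposite-direction responses would push the correlation down instead. For Aim 2 the likely contribution is small. Every size here rests on assumed evoked shares, background correlations and SDs. The direction of the problem, and the immunity of resting-state values and gPPI to it, do not depend on those particular values.

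**What to change.** For the GoNoGo and N-Back runs, do one of the following and say so in the plan:

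1. regress the modelled task responses out of each region's time series before computing the correlations; or
2. use gPPI as the task-connectivity measure.

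Name the chosen measure as the task value carried into Aims 2 and 3, and label any unadjusted task correlation as secondary. If the pipeline already regresses out the task, one sentence saying so, plus naming the measure, is enough. Activation is already an Aim 1 target, so reporting it separately beside connectivity adds no new aim.

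The cost is a short text change and an analysis-pipeline step on scans that are collected anyway. The downside is that residual-based or gPPI estimates are somewhat noisier than raw correlations.

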## Methods and design

### Recruitment and screening

To achieve a target enrollment size of 100, we aim to recruit 125 veterans with pharmacoresistant MDD across sites participating in the VA Clinical TMS Program. This recruitment number (*n*= 125) allows for an anticipated 20% drop out rate of ~ 25 veterans, while still ensuring sufficient statistical power to address the aims of the study. To meet this target, we will recruit approximately 30 veterans per site. We set a minimum of 25 veterans and a maximum of 40 per site to ensure that we retain equivalent site representation. Given the complex nature of the veteran sample, the primary diagnosis of MDD may be comorbid with other disorders, including post-traumatic stress disorder (PTSD).

Veterans will be recruited from four initial preexisting clinics within the Clinical TMS Program: Palo Alto VA Medical Center, White River Junction VA Medical Center, Minneapolis VA Medical Center, and Providence VA Medical Center. All referral sources agree to maintain their clinical relationship with the veterans and attempt to keep medication regimen as stable as possible. Every veteran seen in the TMS Clinical Program will be invited to participate in this study as long as they meet the eligibility criteria. See Table 1 for a summary of the eligibility criteria. The invitation to participate will be extended at the end of the veterans’ initial TMS clinical evaluation with the attending TMS physician. Each veteran’s research involvement is expected to last throughout the course of their clinical TMS treatment.

**Table 1 Tab1:** Inclusion and Exclusion Criteria

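### Aim 1 tests connectivity change against its own baseline with zero as the null value, so regression to the mean alone makes the result significant in most trials with no TMS effect

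*Protocol article*

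**What the plan says.** The Data analysis plan converts connectivity to Fisher Z scores and sets out two Aim 1 tests that relate change to baseline status.

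- A correlation: "Correlational analyses will be used to test whether the extent of early change is proportional to the extent of baseline connectivity impairment".
- A moderator analysis in mixed models, with baseline status entered in binary and continuous form. The question it addresses is: "whether veterans with intact pre-treatment connectivity show connectivity change after early sessions whereas veterans with impaired pre-treatment connectivity show change after completion of sessions".

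The Aim 1 text makes this a study question: "we will systematically test whether the extent of change in connectivity is related to the extent of dysfunction at the pre-stimulation baseline". It also asks "whether early changes in circuit connectivity are necessary, if not sufficient, for subsequent circuit and clinical changes observed post-TMS".

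The Power calculation gives the only session correlation in the document: "With an alpha level of 0.05 (two-tailed), power of 0.875 and an anticipated correlation of 0.5 for repeated sessions we require at least 98 veterans". The section on the lack of a control group says that there is none. Repeat scans of the same subjects are planned under Harmonization of scanners, to measure variation within and between sites. They are not linked to the Aim 1 tests. The limitations do not mention regression to the mean.

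**The concern.** A change score computed from a baseline carries that baseline, including its measurement error and day-to-day variation, with the opposite sign. A veteran whose baseline connectivity happens to read low will tend to read higher next time, whatever the treatment does. Correlating change with baseline, or splitting veterans by baseline and comparing their change, therefore has a null value away from zero. A test against zero treats that displacement as a finding.

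Aim 1 imaging is the primary outcome domain. The article plans to treat dependence of change on baseline as evidence about who responds and when. A test that is significant without any effect cannot supply that evidence. A single-arm design has no untreated group in which the same artefact could be measured and subtracted. Adjusting for sex, medication, medication change, comorbidity, substance use and premorbid function does not uncouple change from baseline. Cross-validation does not help either, because the artefact recurs in every fold.

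**Working it through.** **Inputs.** From the Power calculation: N = 98, two-sided alpha 0.05, rho = 0.5 between sessions, d of about 0.25. Assumed, because the article gives no SDs: equal SD at each session, normal data, no true change, and the same connectivity measure on both sides. Rho is varied, since 0.5 is a general planning value.

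**The plan's own figure.** The recruitment target reproduces: 100/(1 - 0.20) = 125. The required 98 does not reproduce from the stated inputs alone. With d/sqrt(2(1 - rho)) = 0.25/1 = 0.25, a two-sided paired t test at power 0.875 needs 157 (power 0.69 at 98). Reaching 98 needs a standardised change of about 0.317, for instance through covariates that explain part of the variance. That is a separate matter; this point needs only N near 100.

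**Null correlation.** Let B be Baseline and W be 1 Week, each with variance 1.

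- cov(B, W - B) = rho - 1
- var(W - B) = 2(1 - rho)
- corr(B, W - B) = -(1 - rho)/sqrt(2(1 - rho)) = -sqrt((1 - rho)/2)
- At rho = 0.5: -sqrt(0.25) = -0.50

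If impairment is scored in the opposite direction to connectivity, the sign reverses and the size does not.

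**Apparent change after a median split.** The mean of each half of a standard normal lies sqrt(2/pi) = 0.798 from zero, so the spurious shift is 0.798(1 - rho): 0.40 SD at rho 0.5 and 0.16 SD at rho 0.8. The lower half rises and the upper half falls by that amount.

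**Rejection rates with no TMS effect, N = 98, 10,000 simulated trials per row.**

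| rho | expected r | correlation test | median-split test | change vs mean of two scans |
|---|---|---|---|---|
| 0.5 | -0.50 | 99.96% | 99.0% | 5.0% |
| 0.7 | -0.39 | 97.9% | 88.4% | 5.2% |
| 0.8 | -0.32 | 89.0% | 71.4% | 5.0% |
| 0.9 | -0.22 | 60.5% | 42.5% | 4.8% |

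With 80 veterans the correlation test still rejects in 99.8% at rho 0.5. A random-intercept model with all three sessions as outcome rows and baseline as continuous moderator behaves the same way: its 1 Week by baseline term rejects in about 100% of null trials at rho 0.5 and 89% at rho 0.8.

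**Late against early.** Let P be Post-treatment. Then corr(B, P - W) = (corr(B,P) - corr(B,W))/sqrt(2(1 - corr(W,P))).

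- Equal session correlations: the numerator is 0. Simulated rejection is 4.8%.
- Correlation decaying as 0.5 then 0.25: (0.25 - 0.5)/1 = -0.25. Simulated rejection is about 70%.

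**Early against subsequent change.** With equal correlations, cov(W - B, P - W) = rho - 1 and both variances are 2(1 - rho), so the null correlation is -0.50 at any rho. The two changes share the 1 Week scan.

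**The case against.** The arithmetic is hard to contest, but several limits stand.

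- **Timing hypothesis.** A reader might infer that the plan would confirm its whole Aim 1 hypothesis whether or not TMS works. The document does not support that. The hypothesis is a crossover: intact veterans change early, impaired veterans later. Under equal session correlations, regression to the mean acts alike at both follow-up visits and produces no crossover. It also pushes impaired veterans upward at 1 Week, against the expectation that early change is most pronounced in intact veterans.
- **Early and later circuit change.** A reader might infer that early change will be correlated with total change, which shares the baseline. The Data analysis plan fixes no such test. If later change means Post-treatment minus 1 Week, the null correlation is negative and would not look like early change driving later change.
- **Same measure.** This is the natural reading but is not stated. Connectivity comes from rest and two tasks, and the Limitations speak of stratifying on extent of cognitive control or its dysfunction. If impairment came from a measure with independent error, the correlation test would hold its level. Whether Baseline is an outcome row or a covariate in the mixed model is also unstated.
- **Rho.** The 0.5 covers connectivity, behavior and self-report. It is not a reliability estimate for connectivity, so how often the artefact is significant depends on the true value.

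These points narrow the finding. They do not rescue a change-from-baseline test against zero.

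**Conclusion.** The correlation of early change with baseline impairment, and the moderation of each visit's change from baseline by baseline connectivity, are wrong as written when tested against zero. At the plan's rho of 0.5 about 99.9% of null trials would be significant. Even at rho 0.9 the rate is about 60%, twelve times the nominal 5%. The spurious rise in the impaired half, 0.40 SD at rho 0.5, exceeds the planned effect of about 0.25; at rho 0.8 it is 0.16 SD.

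This rests on the same connectivity measure serving as baseline status and as the starting point for change, on equal SDs, and on N near 100. It does not extend to the main effect of session, which the sample size targets. Nor does it extend to the late-minus-early contrast by baseline, provided the sessions correlate equally; if the correlation decays with time, that contrast is affected too.

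**What to change.** State in the analysis plan that neither the baseline-change correlation nor the baseline-by-session term is tested against zero.

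1. **Primary repair.** Relate change to the mean of the two scans (Oldham). State that this assumes equal true variances and is itself inflated if response varies between veterans. With response variation unrelated to baseline of SD 0.3 or 0.5 (assumed values, rho 0.5), it rejects in 8% and 23% of trials.
2. **Sensitivity analysis.** Test the observed slope against the no-change value implied by test-retest correlation. Use the harmonization repeat scans if their number and interval allow; the article states neither. Otherwise report results over a stated range of rho.
3. **Moderator.** Define baseline status from a measure with separate error. For resting state, one run can define status and the other supply change. The two runs have opposed phase encoding, so the split gives up the planned averaging of distortion, and day-level variation remains. The tasks list one acquisition each and have no such split. Use the continuous form for inference.
4. **Crossover.** Test it through Post-treatment minus 1 Week by baseline status, and report the observed session correlations, because the test depends on their being equal.
5. **Early and later circuit change.** Where these are related, note that they share a scan and do not test against zero.

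The cost is analysis wording and noisier single-run estimates. No further veterans are needed. Whether the repeat scans can serve as the benchmark depends on how many there are and how far apart.
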